## Materials and methods

Trial design

The study will employ a two-arm, parallel, single-blinded cluster randomized trial by using multistage sampling to evaluate the effectiveness of X-SIAGA in enhancing household outbreak preparedness against Disease X and outbreaks among the Orang Asli in Selangor. In this two-sided superiority trial design, the intervention group will receive the X-SIAGA intervention and educational brochures, while the control group receives only the brochures. The protocol adheres to the Standard Protocol Items: Recommendations for Interventional Trials (SPIRIT) guideline [22]. The SPIRIT schedule of enrollment, allocation, and assessments is shown in Table 1. 

**Table 1 TAB1:** SPIRIT's schedule of enrolment, interventions, and assessments for X-SIAGA intervention. SPIRIT: Standard Protocol Items: Recommendations for Interventional Trials [22].

	Studt Period					
	Enrolment	Allocation	Post-allocation			
Timepoint	0	0	Baseline Assessment (T_0_)	Immediately Post-intervention (T_1_)	One-Month Post-intervention (T_2_)	Three-Month Post-intervention (T_3_)
Enrollment:						
Eligibility screen	X					
Informed consent		X				
Allocation		X				
Intervention:						
X-SIAGA intervention				X		
Standard educational brochure (control)				X		
Assessments:						
1^st^ questionnaire administration			X			
2^nd^ questionnaire administration				X		
3^rd^ questionnaire administration					X	
4^th^ (final) questionnaire administration						X

Theoretical and conceptual frameworks

This study applied the Social Cognitive Theory (SCT) and the Health Belief Model (HBM) to guide the development and implementation of the X-SIAGA intervention, aiming to influence the Orang Asli’s cognition, health beliefs, and behaviors related to household preparedness for Disease X and outbreaks. SCT is a widely used theory in disaster and emergency health preparedness programs, alongside the HBM. While the HBM focuses mainly on individual beliefs, SCT considers a wider array of factors, highlighting the interaction between behavioral, cognitive, and environmental influences in predicting behavior. Perceived self-efficacy, a cognitive aspect in SCT and part of individual health belief in the HBM, shapes how individuals view their environment and affects their intentions and actions [23].

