Malaysian citizen.	Having severe health conditions (e.g., respiratory and cardiovascular disease requiring oxygen support such as severe asthma, Chronic Obstructive Pulmonary Disease, heart failure and congenital heart diseases).
Age 18 years old and above.	Residing temporarily (less than 2 years).
The head of the household, or the person who contributes to, or influences health-related decisions for the household.	Intending to relocate to a different village within the next 2 years.
Live in a household with more than two members.	
Able to converse, read and write in Malay.	

Sampling, randomization, allocation, and blinding

The study utilizes a multistage sampling approach with computer-generated randomization for the allocation of villages into the intervention or control arm. Due to potential variability in participant numbers and logistical challenges, simple randomization is employed over block randomization for its flexibility and straightforward, unbiased allocation. The entire sampling, randomization, and allocation process is conducted independently by an external health professional with research experience.

First, two districts in Selangor are randomly selected from the eligible pool. Within each district, four villages are randomly chosen. These villages are then divided, with two randomly allocated to the intervention group and two to the control group in each district (i.e., each district has two intervention villages and two control villages). This approach aims to achieve homogeneous sociodemographic groups among the households. Household recruitment in each village is voluntary, facilitated by JAKOA, village leaders, and committees, targeting 12 households per village.

Given the nature of the intervention, the authors are inevitably aware of group allocation. Procedures are identical for both groups, and research assistants are not provided with information about the study sequence or allocation; hence, they remain uninformed about group assignment. Participants in both groups will remain blinded to their allocation throughout the study.

Intervention

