The X-SIAGA intervention package was developed by using the Intervention Mapping framework, and its development process will be reported in a separate publication. Table 4 provides a concise overview of the components and activities included in the X-SIAGA intervention. In the intervention group, households from four Orang Asli villages will receive educational brochures on communicable disease prevention and participate in the X-SIAGA intervention during a one-day program in their respective villages. Two eligible adults from each household will participate in the intervention activities.

**Table 4 TAB4:** Summary of the components and contents of X-SIAGA intervention package.

Component	Contents
Lecture	Introduction to Disease X and outbreak.
	Importance of Household Outbreak Preparedness.
Video presentation	Video presentation on previous outbreaks and discussion.
Experience sharing	Sharing personal experiences with past outbreaks and discussion.
Practical session	Pre-Outbreak: (i) Infection prevention practice: Practicing the 7-step hand hygiene; (ii) Preparedness planning: Developing a household preparedness plan for outbreaks and Disease X.
	During and post-outbreak: (i) Suspecting an outbreak: Recognizing potential symptoms of Disease X and signs of outbreak through a puzzle game; (ii) Outbreak response: Learning what to do in the event of an outbreak through a sequencing game; (iii) Life-saving skills for emergency situations: Performing Hands-Only Cardiopulmonary Resuscitation (CPR).
Simulation exercise	Role-playing three different possible real-life situations: (i) Pre-Outbreak scenario; (ii) During outbreak scenario; (iii) Hands-only CPR scenario.
Game-based learning	“Wabak X” card game play session.

The intervention will be delivered by the authors, assisted by a team of research assistants who are independent of any institutions associated with the authors. All research assistants received prior training and were actively involved at an early stage, including during the pilot phase of the trial.

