Each household will also receive a booklet that includes the materials covered during the X-SIAGA program. Participants start using the booklet during the program, and they take it home for self-study with other family members and to complete their household outbreak preparedness plans. Additionally, they will receive a set of the “Wabak X” card game and are encouraged to play it with their family members. The pair of adults representing their household will complete a questionnaire to assess the change in preparedness scores at all data collection points.

This study aims to assess the effectiveness of X-SIAGA under realistic conditions. This means there will be no refresher sessions or reminders. Instead, only follow-ups at specific time points for data collection will occur. This approach is designed to mirror real-world conditions, as health promotion programs conducted by various local agencies, including government ministries and community organizations, are typically held only once or at most twice per year.

Control

In the control group, households from four Orang Asli villages receive only educational brochures on communicable disease prevention, without the X-SIAGA intervention package. These brochures, sourced from the District Health Office, are currently used by the public health promotion team for education on awareness and prevention of infectious diseases and outbreaks in local communities. Similarly, two eligible adults from each control group household will participate in the research activities and complete the questionnaire at all data collection points. The control group will receive the X-SIAGA intervention package after data collection for all participants is completed.

Data collection

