Data collection will be conducted by using the Household Outbreak Preparedness Evaluation (HOPE) questionnaire, administered at four intervals: (i) before the intervention (T0); (ii) immediately after the intervention, with the intervention group having received both the X-SIAGA intervention and educational brochures and the control group having received educational brochures only (T1); (iii) at one month post-intervention (T2); and (iv) at three months post-intervention (T3). The HOPE questionnaire is an adapted and translated instrument based on prior studies on household preparedness for outbreaks and general disasters [15,24]. Validation of the HOPE questionnaire will be published elsewhere. The questionnaire is self-administered, with assistance available from trained research assistants and representatives of the village committee if participants require support.

Outcome measures

The scoring for the HOPE questionnaire follows Sumaja’s methods [24]. The primary outcome measure, the Household Outbreak Preparedness score, represents the equally weighted average of the Cognitive Preparedness and Preparedness Behavior scores. By using Sumaja’s preparedness matrix [24], scores will be normalized to a scale of zero to one, and a cut-off value of 0.5 at the x- and y-axes will categorize households’ outbreak preparedness into four groups: Fully Prepared, Committed, Aware, and Unprepared.

Secondary outcome measures include the Cognitive Preparedness and Preparedness Behavior scores. The Cognitive Preparedness score assesses household knowledge, attitudes, and health beliefs, while the Preparedness Behavior score evaluates the skills acquired and practices adopted by households to prepare for potential Disease X and outbreaks.

Control of bias

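### The stated blinding of research assistants and participants is contradicted by how the protocol describes delivery, the control arm and recruitment, and every outcome is self-reported

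*Protocol article*

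**What the plan says.** The Abstract and the Trial design section call the study single-blind; the latter describes a "two-arm, parallel, single-blinded cluster randomized trial". The section on sampling, randomization, allocation and blinding accepts that the authors know the allocation and then makes three claims:

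- On those taking part, it promises: "Participants in both groups will remain blinded to their allocation throughout the study".
- On conduct in the two arms, it asserts: "Procedures are identical for both groups".
- On the field staff, it concludes: "research assistants are not provided with information about the study sequence or allocation; hence, they remain uninformed about group assignment".

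The Intervention section states: "The intervention will be delivered by the authors, assisted by a team of research assistants". The Data collection section makes the HOPE questionnaire self-administered, "with assistance available from trained research assistants and representatives of the village committee if participants require support". The Control section gives control households brochures only. The Control of bias section reports that, before recruitment, X-SIAGA was explained to village leaders and committee members, who relayed the information to eligible participants.

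**The concern.** A person who helps run a day-long course in a village knows that the village is in the intervention arm, and so does a person who attends it. Neither fact depends on seeing an allocation list.

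This matters because of the type of outcome. The Outcome measures section builds the primary score as the equally weighted average of a cognitive score (knowledge, attitudes, health beliefs) and a behaviour score (skills and practices). All of it comes from what participants write on a form. With a self-reported outcome the participant is in effect the assessor, so an unblinded participant means an unblinded assessment. A helper who knows the arm adds a second route, through prompting. If the blinding claims are carried into the CONSORT report that the protocol promises, readers would credit the trial with a protection it lacks.

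**Working it through.** No arithmetic bears on this point. The sample-size formula uses the two normal quantiles, the variance, the difference, the cluster size and the intracluster correlation. None of these depends on blinding, so the stated household numbers are unaffected. The check is a comparison of sections.

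1. **Are procedures identical between arms?** The Intervention section and Table 4 describe a one-day village programme with a lecture, a video, experience sharing, practical sessions including CPR, simulation and a card game. Households also take home a booklet and a card set. The Control section gives brochures alone. The arms are visibly different.

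2. **Can assistants be unaware of the arm?** Allocation is by village. The Intervention section has assistants helping to deliver the programme and says that all of them were trained and were involved from the pilot phase. An assistant present at delivery learns that village's arm from the activity itself. Withholding the sequence conceals the arm only until the programme starts.

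3. **Can participants be unaware of their allocation?** Intervention participants attend the programme. The Control of bias section says X-SIAGA was explained to leaders and committees, who passed the information on. A participant who has heard of X-SIAGA knows whether it was received. Even if what was relayed was mainly the confidentiality message, those who attended still know that they attended. At most, participants might be unaware of the study hypothesis, which is a different claim from the one made.

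4. **Is the outcome protected in another way?** HOPE is completed by participants at T0 to T3 and supplies the primary and both secondary outcomes. Help comes from assistants or committee members. The article describes one team of assistants and states no separation between delivery and questionnaire support. T1 falls immediately after the intervention, so delivery staff may still be on site. No outcome has a blinded assessor independent of the participant.

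5. **Is the label consistent?** The trial is called single-blind, yet blinding is claimed for two groups, participants and assistants. On steps 2 and 3, neither claim holds as described.

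**The case against.** The strongest defence is that the claim of identical procedures may refer to assessment only, since both arms complete the same instrument at the same four time points. That reading is available for that one sentence. It does not rescue the statement that participants are blinded to allocation, or the statement that assistants who help with delivery are uninformed.

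Several stronger readings are tempting, and the document does not support them:

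- **That the same individuals deliver the programme and then help with the form.** The article does not say so. It also does not say that they are different people, and a condensed article may omit the roster.
- **That assistants were trained in X-SIAGA specifically, or ran particular sessions.** The text says only that they had prior training and assisted.
- **That controls know they will get the package later.** The Control section says "The control group will receive the X-SIAGA intervention package after data collection for all participants is completed", but not that they are told beforehand.
- **That assistants routinely fill in the questionnaire.** Help is on request, and Table 3 requires participants to read and write Malay, which should limit the need.
- **That every route biases towards X-SIAGA.** Committee members were briefed before recruitment and may help with forms, with no distinction by arm described for either. That route is not shown to be differential.

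The article also admits that the authors are unblinded and lists a possible Hawthorne effect, with assurance that responses carry no penalty. That is a partial acknowledgement of response bias. It does not address reporting that differs by arm, and it leaves the blinding claims standing.

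**Conclusion.** The blinding statements in the Abstract, the Trial design section and the section on sampling, randomization, allocation and blinding are contradicted by the Intervention, Control and Control of bias sections. The design does not have the property it claims.

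Differential reporting by participants, and prompting by helpers who know the arm, are possible at T1, T2 and T3 for all three outcomes. For participants and delivery staff the direction probably favours X-SIAGA. This is a judgement from the nature of the outcome, not something the document establishes. The size cannot be estimated: the document gives no figure for such a bias, and any percentage of the treatment effect would be one assumption divided by another.

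The contradiction itself rests on the text alone. The prompting route rests on the further assumption that delivery and questionnaire roles overlap, which the article leaves open.

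**What to change.** - **Wording.** Withdraw the single-blind label and the two statements that assistants and participants are blinded. Describe participants and delivery staff as unblinded. If participants really are unaware of the hypothesis, say that and no more. Either restrict the sentence on identical procedures to the assessments or remove it.
- **Rostering.** Within the existing team, assign assistants so that those who deliver X-SIAGA in a village do not help with that village's questionnaires. This should hold at least at T2 and T3. At T1 it should apply where staffing allows, because the form follows directly after the programme and a separate helper would have to be on site that day.
- **Help with the form.** Limit help from anyone, including committee members, to reading items aloud from a script, in the same way in both arms.
- **Reporting.** List the remaining self-report bias as a limitation. Rostering reduces prompting but cannot blind participants, so the wording correction is needed in any case.

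The cost is a text correction, a short script, a rostering constraint and a less favourable design label. The sample size and the planned analysis do not change.

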**Figure 2 FIG2:**
[figure not shown]
Conceptual framework. Hypothesis 1 (H1): The intervention changes household preparedness levels, potentially improving their capability to respond to Disease X and potential outbreaks; Hypothesis 2 (H2): The intervention changes cognitive aspects related to preparedness, improving knowledge and attitudes, including health beliefs, towards Disease X and outbreaks; Hypothesis 3 (H3): The intervention changes behavioural aspects related to preparedness, enhancing skills and tangible preparedness practices among households for Disease X and outbreak preparedness.

Study setting and participants

The trial will take place in Orang Asli settlements in Selangor that are gazetted and listed under the Department of Orang Asli Development (JAKOA), focusing on the Orang Asli community members as the study population.

Recruitment

For each selected district, a JAKOA representative is engaged to support the study. The JAKOA representative contacts the village leader of eligible villages to gauge interest in participating. If the village leader expresses interest, an initial meeting is scheduled on a mutually agreed date involving JAKOA, the village leader and committee members, and the research team. During this meeting, the study is explained in detail, and any questions or concerns are addressed. Once the village leader and committee members express their commitment, they are provided with a study information sheet, eligibility criteria, participant expectations, and an ethical information statement.

The study is then promoted by the village leader and committee members to eligible participants. A list of interested and eligible individuals is shared with the research team. The research team prepares a WhatsApp invitation, which is sent to and forwarded by the village leader to the listed participants. Participants who attend the baseline assessment on the agreed date and time are briefed on the study and the consent process. Those who provide written informed consent will complete a baseline assessment and follow their cluster’s assigned intervention. Data collection will commence after participants have signed the informed consent forms.

Sample size

Using the formula for a two-arm parallel-group design in cluster trials [25], the trial requires a minimum sample size of 30 households for each arm. The calculations are as follows:

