\begin{document} m = \frac{(Z_{1-\alpha/2} + Z_{1-\beta})^2 \, 2\sigma^2}{\Delta^2} \left[ 1 + (n - 1)\rho \right] \end{document}

where *m* is the number of households per arm; *Z_1−α/2_* is the standard error associated with a 95% confidence interval (*Z_1−α/2_*=1.96); *Z_1−β_* is the standard error associated with 80% power (*Z_1−β_*=0.842); Δ is the mean awareness score difference between the pre- and post-assessments in the intervention group within a community-based trial on disaster preparedness intervention (Δ=15.97) [26]; σ^2^ is the total variation in awareness score between the pre- and post-assessments in the intervention group within the same trial (σ^2^=138.949) [26]; *n* is the estimated median number of households in Proto-Malay majority Orang Asli villages in Selangor (*n*=54) [18]; and ρ is the intracluster correlation coefficient (ICC) (ρ=0.048) [27].

Allowing for an anticipated attrition rate of approximately 30%, the ideal sample size was set at 45 households per arm. Following the CONSORT Statement recommendation that each study arm should include at least four clusters [28], this study employs multistage sampling to select four Orang Asli villages per arm, aiming for 12 households in each village, a total of 96 households for the study.

Eligibility criteria

Table 2 outlines the eligibility criteria for clusters at both the district and village levels. Meanwhile, Table 3 provides the inclusion and exclusion criteria for participants who will represent their households by participating in X-SIAGA and completing a questionnaire designed to assess the change in preparedness scores at all data collection points.

**Table 2 TAB2:** Eligibility criteria for district and village level clusters.

District	Village
Districts in the state of Selangor.	Villages that have not previously participated in any outbreak preparedness programs.
Districts with gazetted Orang Asli villages.	Villages with more than 12 households.
Districts with more than 5 Orang Asli villages.	Villages accessible via road transport.

**Table 3 TAB3:** Inclusion and exclusion criteria of participants.

Inclusion criteria	Exclusion criteria
Orang Asli descent.	Having physical or cognitive disabilities (e.g., blindness, deafness, schizophrenia and dementia).

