To prevent contamination bias, the study ensures sufficient geographical separation between intervention and control villages to minimize interactions among participants from different groups. Prior to recruitment, the research team held meetings with village leaders and committee members, in the presence of JAKOA officials, to explain the X-SIAGA intervention, emphasize the importance of strict confidentiality, and discourage discussions about the intervention. These leaders and committee members then conveyed this information to eligible participants during household recruitment. All participants will again receive a detailed explanation of the privacy and confidentiality policy when expressing interest in joining the trial, and only those who provide consent will be enrolled. To mitigate attrition bias, the study will employ an Intention-to-Treat (ITT) approach. Additionally, to sustain motivation and engagement, perishable goods will be offered as incentives at each stage of data collection.

Statistical methods

The statistical analysis for this study will be carried out by using the IBM SPSS Statistics for Windows, Version 26 (Released 2018; IBM Corp., Armonk, New York). Descriptive statistics will include frequency and percentages for categorical data and mean and standard deviation for numerical data.

To compare baseline sociodemographic characteristics between the intervention and control groups, a Pearson Chi-Square test will be utilized for categorical variables, while an Independent Samples t-test will be used for continuous variables. To evaluate changes over time from T0 to T3 between and within the groups, a repeated-measures analysis of variance will be conducted. To assess variation in results between and within the groups across the different time points, while also controlling for potential confounding variables, a generalized estimating equation will be utilized.

Statistical analyses will use a two-tailed test to evaluate the superiority hypothesis. The null hypothesis states that there is no difference between the X-SIAGA intervention package and standard educational brochures. A significance level of 0.05 will be applied.

Data management

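### Two adults answer for each household but no unit of analysis is stated, and the named repeated-measures ANOVA has neither a household nor a village level

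*Protocol article*

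**What the plan says.** **Respondents.** The Intervention section brings two eligible adults from each household into the programme and states: "The pair of adults representing their household will complete a questionnaire to assess the change in preparedness scores at all data collection points". The Control section says: "two eligible adults from each control group household will participate in the research activities and complete the questionnaire at all data collection points". Data collection describes the questionnaire as self-administered.

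**Unit of design and outcome.** Under Sample size, "the trial requires a minimum sample size of 30 households for each arm". This becomes 45 after attrition, and the plan is 12 households in each of 8 villages, 96 in all. Outcome measures defines the primary score as the equally weighted average of the cognitive and behaviour scores and places households in four categories. That weighting combines two domains, not two respondents. The section on theoretical and conceptual frameworks defines the cognitive half as something an individual person holds.

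**Analysis.** Villages are randomised. Under Statistical methods, "a repeated-measures analysis of variance will be conducted" for change from T0 to T3, and a GEE is added for the same comparisons with confounder adjustment. Neither is given a unit of analysis or a clustering level. "Statistical analyses will use a two-tailed test to evaluate the superiority hypothesis", and "A significance level of 0.05 will be applied".

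**The concern.** Two relatives living together are likely to give similar answers about knowledge, beliefs and household practices. If each adult's form becomes a row and the test has no household level, the 96 adults per arm are counted as 96 independent pieces of information when they carry less. Standard errors are then too small and the nominal 5% level is not kept.

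The same weakness exists one level up. Allocation is by village, and a repeated-measures ANOVA with only arm and time as factors takes its rows as independent between subjects. So even if the pair is reduced to one household row, the named test ignores the unit that was randomised. What is at stake is the validity of the p-value and confidence interval for the primary comparison, and whether the analysed unit matches the one used for the sample size.

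**Working it through.** **1. The plan's own figure.** Inputs from Sample size: z-values 1.96 and 0.842, Δ = 15.97, σ² = 138.949, n = 54, ρ = 0.048.

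- Unclustered: (1.96 + 0.842)² × 2 × 138.949 / 15.97² = 8.555
- Design effect: 1 + (54 − 1) × 0.048 = 3.544
- Product: 8.555 × 3.544 = 30.32

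This reproduces the stated 30 households per arm. The formula counts households and carries a single ICC, so no within-household correlation enters it.

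**2. Set-up for the check.** From the plan: 4 villages × 12 households × 2 adults = 96 adults per arm, village ICC 0.048, two-sided 5%. Assumed, because the article gives no value: within-household correlation r = 0.3, 0.5 or 0.7. The test is a two-group comparison at one time point. Its true error is approximately 2 × [1 − Φ(1.96/√DE)], where DE is the variance inflation that the test ignores. Each case was also simulated with 20,000 null trials.

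**3. Adult rows, pairing alone.** DE = 1 + r.

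| r | DE | 96 adults are worth | error, formula | error, simulated |
|---|---|---|---|---|
| 0.3 | 1.3 | 74 | 8.6% | 8.3% |
| 0.5 | 1.5 | 64 | 11.0% | 11.0% |
| 0.7 | 1.7 | 56 | 13.3% | 13.5% |

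**4. Adult rows, village also ignored.** Each adult shares a village with 22 adults from other households, so DE = 1 + r + 22 × 0.048.

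| r | DE | error, formula | error, simulated |
|---|---|---|---|
| 0.3 | 2.356 | 20.2% | 20.4% |
| 0.5 | 2.556 | 22.0% | 22.4% |
| 0.7 | 2.756 | 23.8% | 24.6% |

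**5. One mean per household, village ignored.** Averaging reduces the total variance to (1 + r)/2, so the ICC of the household mean is 0.048 / [(1 + r)/2], and DE = 1 + 11 × that value.

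| r | ICC of household mean | DE | error, formula | error, simulated |
|---|---|---|---|---|
| 0.3 | 0.074 | 1.812 | 14.5% | 14.8% |
| 0.5 | 0.064 | 1.704 | 13.3% | 13.5% |
| 0.7 | 0.056 | 1.621 | 12.4% | 12.9% |

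If 0.048 is instead taken as the ICC of the household score itself, DE = 1 + 11 × 0.048 = 1.528 and the error is about 11%.

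**6. The correct levels.** With no village clustering, household means give 4.7-5.4% (simulated), so the pairing inflation disappears. With the village ICC present, a t-test on the eight village means gives 5.1-5.2%.

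**The case against.** Several counter-arguments are fair.

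- *The pair may complete one joint form.* The intervention wording speaks of a pair and a single questionnaire, so this is possible. Self-administration, the control-arm wording and a cognitive score defined for a person favour one form each, but do not settle it. Under a joint form the pairing inflation is zero.
- *Every stated unit is the household.* The outcome definition does imply a household row, and one averaged score would also remove the pairing inflation. It would not remove the village component in step 5.
- *A GEE is planned.* It can handle correlated data if clustered on household or village. The article does not say which, and it names the repeated-measures ANOVA for the same comparisons.
- *The figures are not for the planned test.* Correct. They come from a single-time comparison. Stable household and village effects cancel from a group-by-time contrast, so the inflation there depends on how far changes from T0 correlate within household and village.
- *Such detail belongs in an analysis plan that is not shown.* By itself, a missing rule for combining two respondents could be left there. A named test that omits the randomised unit is a choice made in this document.

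A reader might also infer four things that the article does not support. It does not say that adult rows will be analysed as independent. The t-test and chi-square do not bear on the outcome, because they are confined to baseline characteristics. Table 3 does not fail to provide for a second adult: its role criterion is worded in the singular ("The head of the household, or the person who contributes to, or influences health-related decisions for the household"), but it applies to each participant, more than one household member can influence health decisions, and the Intervention and Control sections already require two eligible adults. Finally, the 20-25% is not the cost of pairing, since it includes ignored village clustering.

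**Conclusion.** The point stands in limited form. Two respondents per household feed a household-level outcome and sample size with no stated link, and the repeated-measures ANOVA has no level for household or village. In a single-time two-group comparison at nominal 5%, the ANOVA's independence assumption would cost:

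- about 8-14% error from pairing alone if each adult is a row (zero with a joint or averaged score);
- about 20-25% if village is also ignored;
- about 13-15% with household means that ignore village.

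The named test is therefore unsound on either reading of the questionnaire. The pairing figures rest on an assumed correlation of 0.3-0.7, and the village figures on the plan's ICC of 0.048. They do not measure the inflation in the group-by-time test, which needs correlations of change that the article does not give. The figure of 30 households per arm is unaffected, because it already counts households.

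**What to change.** In Outcome measures, state that the household is the unit of analysis, and that each score at each visit is the mean of the two adults' normalised scores, or the single available adult's score when only one responds. That gives one row per household and visit. Say how this fits the last-observation-carried-forward rule in Data management, which does not specify whether a dropout is an adult or a household. If a joint form is intended, say so.

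In Statistical methods, replace the repeated-measures ANOVA as the primary test by one of:

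- a model or GEE on household rows, clustered on village, with a small-sample correction for eight clusters;
- an analysis of village-level summaries;
- a model that keeps both adults, with household nested in village.

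Table 3 needs no change. The cost is a few sentences, settled before outcome data are seen, and less favourable apparent precision: with eight villages a village-level comparison has only 8 − 2 = 6 degrees of freedom.
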